### Power Analysis

We anticipate recruiting 180 families, allowing for a 20% attrition rate and resulting in a final goal of completing the trial with at least 144 families. We assessed power using a simulation study; each simulated dataset contained 40 clusters (20 REDCHiP, 20 attention control intervention) of 4 to 5 participants each. We simulated posttreatment scores using the following model: Y_ij_ = rX_ij_ + u_i_ + ES×Condition_i_ + ε_ij_, where Y_ij_ is the posttreatment score for the *j*th participant in the *i*th cluster, r is the within-cluster correlation between baseline and posttreatment scores (set to .72 based on pilot data), X_ij_ is the *ij*th participant’s baseline score, u_i_ is the normally distributed random intercept for the *i*th cluster, ES is the standardized effect size (set to 0.6 standard deviations based on pilot data), Condition is an indicator (1 for REDCHiP, 0 for attention control intervention), and ε is a normally distributed error term. The variances of u_i_ and ε_ij_ were set to yield a within-condition intraclass correlation coefficient of .10. We fit a mixed model with a random cluster intercept and baseline score and condition as predictors to each of 1000 simulated data sets. To compute estimated power we took the average number of data sets for which the condition was statistically significant in a 2-sided test at α=.05. Based on the indicated parameter values and sample size, estimated power was 83%. For 40 groups averaging 3.6 families each, estimated power was 90%. Recognizing this trial will include a control group, which could attenuate our REDCHiP effect, if we conservatively reduce the standardized effect size to 0.4 standard deviations, estimated power is 85%.

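### The three stated power figures (83%, 90% and 85%) cannot all come from the one simulation described

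*Protocol article*

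**What the plan says.** All the figures are in the Power Analysis section of the protocol article. The simulated design is described as "each simulated dataset contained 40 clusters (20 REDCHiP, 20 attention control intervention) of 4 to 5 participants each", about 180 families. The effect is defined so that "ES is the standardized effect size (set to 0.6 standard deviations based on pilot data"), and the baseline coefficient so that "r is the within-cluster correlation between baseline and posttreatment scores (set to .72 based on pilot data"). The variances of the cluster intercept and the error term "were set to yield a within-condition intraclass correlation coefficient of .10"; their absolute values are not given. Power is the share of 1000 data sets in which "the condition was statistically significant in a 2-sided test at α=.05".

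Three results follow. The first two are given together: "Based on the indicated parameter values and sample size, estimated power was 83%. For 40 groups averaging 3.6 families each, estimated power was 90" (per cent). Here 40 × 3.6 = 144 is the completer target, and no other parameter is said to change between the two. Last, to allow for attenuation by the control group, "if we conservatively reduce the standardized effect size to 0.4 standard deviations, estimated power is 85" (per cent); the cluster size behind this figure is not restated.

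**The concern.** Two comparisons run the wrong way. Fewer families in the same number of clusters are credited with more power (83% to 90%). An effect one third smaller is credited with 85%, above the 83% given for the full effect and only 5 points below the 90%.

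These figures are the only quantitative support in the article for recruiting 180 families. The 85% also carries the reassurance that an attention control will not leave the trial short of power. While the three figures disagree, a reader cannot tell which to rely on, or how to interpret a null result if the true effect is nearer 0.4 SD.

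**Working it through.** **Inputs (Power Analysis section).** Two-sided α = .05; 20 clusters per arm; mean cluster size m = 4.5 (180 families) or 3.6 (144); r = .72, so 1 − r² = .4816; ICC = .10; effect (ES) 0.6 or 0.4. The variances var_u (cluster intercept) and var_e (error) are not stated. The effect is carried forward to the 90% figure, and both sizes are tried for the 85% figure.

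**Formula.** SE = √[(var_u + var_e/m) × 4/40]; power ≈ Φ(ES/SE − 1.96). A noncentral t version on 38 df was also run.

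**Check 1: cluster size.** With ICC .10 on the residual, SE² is proportional to .10 + .90/m, which is .300 at m = 4.5 and .350 at m = 3.6. The SE therefore grows by √(.350/.300) = 1.08 in the smaller sample, whatever the absolute variances. 83% corresponds to ES/SE = 1.96 + .954 = 2.914. Dividing by 1.08 gives 2.698, a power of about 77%, not 90%. The direction holds for any positive var_e. The Monte Carlo SEs are √(.83 × .17/1000) = 1.2 points and √(.90 × .10/1000) = 0.9 points, so the SE of the difference is about 1.5 points against a gap of 7.

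**Check 2: effect size.** At a fixed design, ES/SE scales with ES.
- 85% at 0.4: ES/SE = 2.996; × 1.5 = 4.495; power at 0.6 is 99.4%.
- 90% at 0.6: ES/SE = 3.242; × 2/3 = 2.161; power at 0.4 is 58%.
- 83% at 0.6: ES/SE = 2.914; × 2/3 = 1.943; power at 0.4 is 49%.

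Letting the 85% refer to the other cluster size does not help. 85% at 0.4 SD with 180 families would still imply 98.6% at 0.6 SD with 144 (2.996 × 1.5/1.08 = 4.16).

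**Check 3: can any scaling reproduce the figures?** Closed-form power in per cent, t to normal version:

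| Scaling | var_u | var_e | 0.6, n=180 | 0.6, n=144 | 0.4, n=180 | 0.4, n=144 |
|---|---|---|---|---|---|---|
| 1. Outcome variance 1, ICC on residual | .048 | .433 | >99 | >99 | 90–91 | 85–87 |
| 2. Outcome variance 1, ICC as share of total | .100 | .382 | 99 | 98–99 | 82–84 | 78–80 |
| 3. var_e = 1 − r² (r strictly within cluster), ICC on residual | .054 | .482 | >99 | 99 | 87–88 | 81–83 |
| 4. As 3, ICC as share of total | .111 | .482 | 98 | 96–97 | 75–77 | 70–72 |
| 5. var_u + var_e = 1 | .100 | .900 | 92–93 | 88–89 | 61–64 | 55–57 |
| 6. var_e = 1, var_u 10% of total | .169 | 1.000 | 84–86 | 79–81 | 50–53 | 45–47 |
| **Stated** | | | **83** | **90** | **85 (n not given)** | **85 (n not given)** |

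Simulations of the stated model (REML random-intercept fit, 2000 data sets per cell) for scalings 1, 2, 5 and 6 agree to within about 2 points. For example, scaling 1 at 0.4 SD gives 88–89% with 180 families and 84–86% with 144.

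No row gives more than one of the three figures. The 85% matches scaling 1 at 144 families. The 90% is approached only by scaling 5 (simulated 86–87%), and the 83% only by scaling 6. Solving each stated figure for the residual variance at ICC .10 gives 1.41 (the 83%), 0.98 (the 90%), and 0.51 or 0.59 (the 85%, with 144 or 180 families): three incompatible scales.

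**Check 4: which scales fit the text?** With a standardized baseline and residual variance 1, the implied correlation is .72/√(.5184 + 1) = .58, not .72. Scalings 5 and 6 therefore fit poorly; scalings 1 to 4 keep r as a correlation.

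**The case against.** The section does not repeat the effect size beside the 90% or the cluster size beside the 85%, so an unstated parameter might have changed between results. That is possible, but the text gives no other value, and both designs it describes have 40 clusters. As printed, a reader can only carry the values forward.

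A simple transposition of 83% and 90% is the most natural innocent explanation. It nearly repairs the first pair, since 90% at m = 4.5 implies about 85% at m = 3.6. It does not repair the third figure, because 90% at 0.6 SD still implies about 58% at 0.4 SD for the same design.

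The strongest counter-argument concerns consequence, and much of it stands. A reader might infer from the 90% that the trial is badly underpowered at 0.4 SD, with power near 55%. The document does not support this. That value needs a residual variance near 1, whose only backing is one of the figures in dispute and which contradicts the stated correlation. Readings that respect the stated r and effect units give 70% or more at 0.4 SD, and the one that matches the printed 85% is a natural reading of the text. The attrition arithmetic (180 × 0.8 = 144) is also correct.

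**Conclusion.** The contradiction is certain and does not depend on the unstated variances: the three figures cannot come from one simulation as described. Its effect on the trial is less certain and probably modest. Taking r as a correlation and the effect in outcome SDs, power at 0.6 SD is about 96% to over 99%. At 0.4 SD it is about 70–87% with 144 families analysed and 75–91% with 180; the spread comes from how the ICC and the within-cluster correlation are read. On that basis the 85% may be correct, with the 83% and 90% too low. Power at 0.4 SD drops to about 55–64% with residual variance near 1, and lower still on the larger scale that the 83% would imply, but neither scale is consistent with r = .72 and a standardized baseline. The supported conclusion is that the power statement must be recomputed, not that the trial is too small.

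**What to change.** Rerun the simulation under a single scaling. State the variances of the baseline score, the cluster intercept and the error term, and say whether the ICC refers to the residual or the total variance. Replace the three figures with one table: power at 0.6 and 0.4 SD, each for 40 clusters averaging 4.5 (180 families) and 3.6 (144 families). Under scaling 1 the entries would be above 99% at 0.6 SD, and about 90% (180) and 85% (144) at 0.4 SD. If the investigators find that the effect was in fact expressed in residual SDs, the 0.4 SD entries must be restated at about 55–64%.

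The cost is a rerun of existing code and a correction of one paragraph. The repair requires no change in enrolment and no choice of a single outcome.

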## Results

Recruitment began in July 2019, and enrollment is ongoing. The first wave of the intervention began in December 2019. We anticipate completing enrollment in 2023. Final reporting of results will occur within 12 months of the primary completion date.

## Discussion

### Limitations

This trial will focus on families of young children with T1D and exclude children who are on conventional insulin therapy, which could limit some of its generalizability. However, we anticipate little negative impact from this decision because intensive insulin therapy is now the gold standard regimen for individuals with T1D. An examination of maintenance effects of REDCHiP up to 3 months’ posttreatment will occur, but we will not be able to draw inferences regarding longer term effects. Our trial includes numerous outcome measures, which increases the risk of missing data. We have attempted to reduce the risk of missing data through device use (eg, accelerometry to measure physical activity and sleep) and online questionnaire access and data sharing. We intend to give caregivers free and accessible technology support before and during telehealth visits in order to reduce any disruptions due to difficulties with the telehealth platform. We intend to stratify our samples according to child sex, age, and CGM status to control for any effect of these variables in our final models. Yet there may be other demographic variables we will not be able to control for a priori that moderate caregiver fear of hypoglycemia, and we may need to adjust for those in our final analyses. In addition, we intend to identify whether young children are using a hybrid closed loop or predictive low-glucose management system via caregiver report or electronic health record review and may adjust for these variables in our final analyses.

### Conclusions

Our experience studying fear of hypoglycemia in families of young children with T1D reveals that this is a common fear for caregivers that is related to poorer quality of life and suboptimal child glycemic control. Our initial pilot study revealed promising effects for using cognitive behavioral techniques and a group-based telehealth approach to reduce caregiver fear of hypoglycemia. If this larger, multisite trial confirms the efficacy of REDCHiP and the acceptability and feasibility of our telehealth delivery method, future directions will focus on widespread dissemination of the REDCHiP intervention and implementation across a variety of clinic settings.

## Abbreviations

CGM: continuous glucose monitor
HbA_1c_: glycated hemoglobin
HIPAA: Health Insurance Portability and Accountability Act
IRB: institutional review board
REDCap: Research Electronic Data Capture
REDCHiP: Reducing Emotional Distress for Childhood Hypoglycemia in Parents
T1D: type 1 diabetes mellitus
